## Abstract

**Background:** High blood pressure (BP), particularly systolic BP (SBP), is the major modifiable risk factor for cardiovascular diseases and related disorders of aging. SBP increases markedly with aging in women such that the prevalence of above-normal SBP (i.e., ≥120 mmHg) in postmenopausal women exceeds rates in age-matched men. This increase in SBP is associated with vascular endothelial dysfunction, mediated by excessive reactive oxygen species-induced oxidative stress and consequent reductions in nitric oxide bioavailability. Moderate-intensity aerobic exercise is a recommended lifestyle strategy for reducing SBP. However, adherence to aerobic exercise guidelines among postmenopausal women is low (<30%) and aerobic exercise does not consistently enhance endothelial function in estrogen-deficient postmenopausal women. High-resistance inspiratory muscle strength training (IMST) is a time-efficient, adherable lifestyle intervention that involves inhaling against resistance through a handheld device (30 breaths/day). Here, we present the protocol for a randomized controlled trial investigating the efficacy of 3 months of high-resistance IMST compared to guideline-based, “standard-of-care” aerobic exercise training for decreasing SBP and improving endothelial function in estrogen-deficient postmenopausal women with above-normal SBP (120–159 mmHg) at baseline (ClinicalTrials.gov Identifier: NCT05000515).

**Methods:** A randomized, single-blind, parallel-group design clinical trial will be conducted in 72 (36/group) estrogen-deficient postmenopausal women with above-normal SBP. Participants will complete baseline testing and then be randomized to either 3 months of high-resistance IMST (30 breaths/day, 6 days/week, 75% maximal inspiratory pressure) or moderate-intensity aerobic exercise training (brisk walking 25 min/day, 6 days/week, 40–60% heart rate reserve). Outcome measures will be assessed after 3 months of either intervention. Following end-intervention testing, participants will abstain from their assigned intervention for 6 weeks, after which BP and endothelial function will be assessed to evaluate the potential persistent effects of the intervention on the primary and secondary outcomes.

**Discussion:** This study is designed to compare the effectiveness of time-efficient, high-resistance IMST to guideline-based aerobic exercise training for lowering SBP and improving endothelial function, and interrogating potential mechanisms of action, in estrogen-deficient postmenopausal women.

**Clinical Trial Registration:**
ClinicalTrials.gov, Identifier: NCT05000515.

## Introduction

### Background and rationale

Above-normal casual (resting) blood pressure (BP), defined as systolic BP (SBP) ≥120 mmHg and/or diastolic BP (DBP) ≥80 mmHg (Whelton et al., 2018), increases the risk of developing cardiovascular diseases (CVD) and other chronic health conditions (Kivipelto et al., 2001; Guo et al., 2013; Huang et al., 2013, 2014).

In adults aged 50 years and older, the disease risks of high BP are driven primarily by above-normal SBP, as DBP plateaus at midlife and then actually decreases at older ages (Franklin et al., 1997). Absolute SBP levels are lower in premenopausal women compared to age-matched men. However, SBP increases more rapidly in women after the menopausal transition, such that the prevalence of above-normal SBP in postmenopausal women meets and then exceeds rates observed in age-matched men (Ji et al., 2020; Tsao et al., 2022).

This greater increase in SBP in postmenopausal women plays a key role in the increased risk of CVD, including stroke, heart failure with preserved ejection fraction, and other cardiovascular complications in older women compared to men (Beale et al., 2018; Tsao et al., 2022).

Currently, >75% of postmenopausal women in the United States have above-normal SBP (Abramson et al., 2018; Whelton et al., 2018) and the number of postmenopausal women is expected to grow by 37% by the year 2060 (United States Census Bureau, 2017). In addition, established treatments for lowering and controlling SBP are less effective in postmenopausal women compared to men (Lloyd-Jones et al., 2005; Pimenta, 2012). Thus, establishing novel strategies for lowering SBP in postmenopausal women is a biomedical research priority.

Increasing SBP is closely linked to impaired vascular endothelial function (Buford, 2016). Compared to their normotensive peers, postmenopausal women with above-normal SBP demonstrate impaired endothelium-dependent dilation (Craighead et al., 2020), an independent predictor of CVD (Inaba et al., 2010; Green et al., 2011; Ras et al., 2013; Xu et al., 2014; Matsuzawa et al., 2015). This endothelial dysfunction is driven by oxidative stress-mediated suppression of the bioavailability of nitric oxide (NO), a critical vasodilatory molecule (Doshi et al., 2001; Seals et al., 2011).

SBP-lowering therapies that concomitantly improve vascular endothelial function are superior for reducing CVD risk compared to therapies that have isolated effects on SBP (Modena et al., 2002; Kitta et al., 2009). Therefore, interventions that both lower SBP and improve vascular endothelial function hold strong promise for disease prevention in postmenopausal women.

Among other health benefits, regular moderate-intensity aerobic exercise is a recommended lifestyle intervention for lowering SBP (Whelton et al., 2018). However, only 25–30% of postmenopausal women in the United States meet guidelines for 150 min/week of moderate-intensity aerobic exercise (Keadle et al., 2016; Bennie et al., 2019). The most commonly cited barrier contributing to this low rate of adherence is lack of time (Stutts, 2002; El Ansari and Lovell, 2009; Kelly et al., 2016). Other common barriers include facility access, mobility issues, and financial cost (Yarwood et al., 2005; Siddiqi et al., 2011; Babakus and Thompson, 2012; Kelly et al., 2016).

Along with SBP-lowering effects, aerobic exercise also improves vascular endothelial function in midlife/older men (DeSouza et al., 2000; Pierce et al., 2011b), but does not consistently induce the same benefits in estrogen-deficient postmenopausal women (i.e., women not taking hormone therapy) (Pierce et al., 2011b; Moreau et al., 2013; Santos-Parker et al., 2017), a group that makes up over 90% of the postmenopausal women in the United States (Connelly et al., 2000).

This is due to the inability of aerobic exercise to reduce oxidative stress in women deplete of estrogen (Moreau et al., 2013). Estrogen repletion through hormone therapy prior to training restores the beneficial effects of aerobic exercise on the vascular endothelium in postmenopausal women (Moreau et al., 2013). However, hormone therapy is contraindicated in most cases and not a viable option for enhancing the effects of aerobic exercise in postmenopausal women (Rossouw et al., 2002). As such, developing novel lifestyle interventions that promote adherence, lower SBP, and improve endothelial function in estrogen-deficient postmenopausal women is a biomedical research priority (Seals et al., 2019).

One such potential intervention is high-resistance inspiratory muscle strength training (IMST), which involves breathing in against resistance through a handheld device (Craighead et al., 2019). In contrast to conventional inspiratory muscle training against low-to-moderate levels of resistance performed for extended durations, high-resistance IMST utilizes a low number of repetitions against a near-maximal resistance, resulting in a daily time commitment of only approximately 5 min, overcoming the critical time-availability barrier (Craighead et al., 2021a). Additionally, by using an affordable, portable device, high-resistance IMST overcomes many common barriers associated with aerobic exercise and holds promise for future public health translation (Craighead et al., 2022). However, the efficacy of high-resistance IMST for inducing cardiovascular health benefits, particularly in estrogen-deficient postmenopausal women, needs to be firmly established.

We recently completed a pilot study in midlife/older men and women (aged 50–79 years) with above-normal initial SBP comparing 6 weeks of high-resistance IMST (30 breaths/day, 6 days/week, 75% maximal inspiratory pressure [PI_MAX_]) to low-resistance (15% PI_MAX_) sham control training. IMST was safe (no serious adverse events), tolerable (no dropouts due to adverse events) and promoted adherence (94% of prescribed training sessions performed) (Craighead et al., 2021b).

In this pilot trial, IMST also induced clinically meaningful improvements in cardiovascular function. Casual SBP was reduced by 9 mmHg and this reduction was ∼75% sustained 6 weeks after completing the last IMST training session; casual DBP also was reduced by 2 mmHg. Twenty-four-hour SBP, a CVD risk factor independent of casual SBP (Clement et al., 2003; Dolan et al., 2005), decreased by 4 mmHg. Brachial artery flow-mediated dilation (FMD_BA_), a measure of endothelial function, was increased by approximately 45%. Improvements in cardiovascular function were associated with reductions in oxidative stress and increased NO bioavailability (Craighead et al., 2021b).

Although establishing the sex-specific effects of IMST was not a primary objective of our trial due to a limited sample size, our initial results suggested IMST was at least equally as effective for lowering SBP and improving endothelial function in estrogen-deficient postmenopausal women as in age-matched men (Craighead et al., 2021b).

To extend these encouraging preliminary results from our pilot trial and establish the efficacy of high-resistance IMST in estrogen-deficient postmenopausal women, we are conducting a randomized, single-blind, parallel group design clinical trial seeking to investigate the comparative effectiveness of high-resistance IMST versus moderate-intensity aerobic exercise for 1) lowering casual and 24-h SBP; 2) improving vascular endothelial function; and 3) beneficially modulating oxidative stress and NO bioavailability in estrogen-deficient postmenopausal women with initial above-normal SBP (120–159 mmHg) (Figure 1).

**FIGURE 1 F1:**
[figure not shown]
Hypothesis. Hypothesized effects of high-resistance inspiratory muscle strength training for lowering systolic blood pressure and improving endothelial function to a greater extent than guideline-based moderate-intensity aerobic exercise in estrogen-deficient postmenopausal women. E2, estrogen; BP, blood pressure; NO, nitric oxide; ROS, reactive oxygen species.

We also will further assess the safety and tolerability of, and adherence to, the interventions. Potential persistent effects of the interventions on cardiovascular function following abstention also will be examined.

We will address these aims by assessing our outcome measures before and at the end of 3 months of high-resistance IMST (30 breaths/day, 6 days/week, 75% PI_MAX_) or guideline-based aerobic exercise (150 min/week brisk walking), and 6 weeks after stopping the interventions, in estrogen-deficient postmenopausal women with above-normal initial SBP.

## Methods

### Study design

This is a randomized, single-blind, parallel-group design clinical trial assessing 3 months of high-resistance IMST versus moderate-intensity aerobic exercise (brisk walking) in 72 (36/group) estrogen-deficient postmenopausal women with above-normal SBP at baseline. The intervention duration for the current protocol was chosen based on clinical guidelines for lifestyle-based treatment of high BP, which recommend 3 months of healthy lifestyle practices as a first-line intervention for lowering BP (Whelton et al., 2018).

Postmenopausal women with SBP 120–159 mmHg who have not taken hormone therapies within the previous 12 months will be eligible to participate provided they meet all criteria for inclusion and exclusion (Table 1).

**TABLE 1 T1:** **|** Inclusion and exclusion criteria.

Inclusion criteria	Exclusion criteria
• Postmenopausal women (>12 months of amenorrhea)	• Early menopause (menopause before age 45 years)
• Estrogen deficient (no hormone therapies within the previous 12 months)	• Having had a hysterectomy or oophorectomy
• Age 50 years or older	• Current smoker
• Ability to provide informed consent	• Chronic overt medical condition (e.g., recent myocardial infarction or stroke, cancer, diabetes)
• Willing to accept random assignment to condition	• Alcohol abuse or dependence
• SBP 120–159 mmHg	• Uncontrolled thyroid disease or change in thyroid medication within previous 3 months
• Body mass index <40 kg/m^2^	• History of uncontrolled hypertension (SBP >180 mmHg and/or DBP >120 mmHg)
• Weight stable in the prior 3 months (<2 kg weight change) and willing to remain weight stable throughout the study	• Abnormal BP response to exercise (drop in SBP below resting pressure or SBP >260 mmHg or DBP >115 mmHg)
• Absence of clinical disease as determined by medical history, physical examination, blood chemistries, ankle-brachial index, and 12-lead ECG	• Regular vigorous aerobic/endurance exercise (>4 bouts/week, >30 min/bout at a workload >6 METS)
Ankle-brachial index >0.7	
Total cholesterol <240 mg/dl	• Blood donation within 8 weeks prior to enrolling in the study; unwilling to abstain from donating blood for 8 weeks after completing the study
Fasting plasma glucose <126 mg/dl	
Normal 12-lead ECG at rest and during graded treadmill exercise to fatigue	
• Subjects taking antihypertensive medications will be included provided they meet the other inclusion criteria, including SBP. Medication regimen (prescription and dosing) must be stable for at least 3 months prior to enrollment in the study and must remain stable during the study	

SBP, systolic blood pressure; DBP, diastolic blood pressure; ECG, electrocardiogram; METs, metabolic equivalents.

### Outcomes

All outcomes will be measured before and after 3 months of high-resistance IMST or moderate-intensity aerobic exercise. Casual SBP, 24-h SBP and FMD_BA_ also will be measured 6 weeks after cessation of IMST and aerobic exercise to determine the long-lasting effects of IMST on our primary and secondary outcome measures.

All cardiovascular measurements and blood sampling will be performed after a >5-h fast from food (water allowed) and caffeine, >24-h abstention from alcohol and vigorous physical activity, and >48-h abstention from dietary supplements and over-the-counter medications. Supervised training sessions and check-in visits will be performed without dietary, medication, or activity restrictions.

### Primary outcome

#### Casual (resting) systolic blood pressure

Casual (resting) SBP will be measured and classified according to 2017 American College of Cardiology/American Heart Association guidelines (Whelton et al., 2018). Subjects will rest quietly for at least 5 min while seated with their back supported, feet flat on the floor, and arm at heart level. BP will be measured in triplicate, with a 2-min recovery between each measure, over the brachial artery of the non-dominant arm via automated oscillometric sphygmomanometer (Mindray), validated according to the Association for the Advancement of Medical Instrumentation standards (Anwar et al., 1997) and regularly calibrated by the manufacturer.

During baseline, end-intervention, and follow-up testing, casual BP will be measured on two separate days, >24 h apart, and casual SBP and DBP will be defined as the average over the 2 days. Casual SBP and DBP also will be measured at a single timepoint during each supervised training session and check-in visit (Figure 2) to monitor changes in BP across the intervention.

**FIGURE 2 F2:**
[figure not shown]
Study design. IMST, inspiratory muscle strength training; AE, aerobic exercise; PI_MAX_, maximal inspiratory pressure.

### Secondary outcomes

#### 24-Hour ambulatory systolic blood pressure

Brachial artery BP will be measured every 20 min during the day (16-h period) and every 60 min at night (8-h period) over 24 h according to each participant’s individual self-reported sleep-wake cycle.

BP will be measured via ambulatory BP monitoring (Oscar 2, SunTech Medical), validated according to British Hypertension Society standards (Goodwin et al., 2007). Participants will be outfitted with the ambulatory BP monitor by a trained investigator and given written and verbal instructions regarding monitor operation. The BP cuff will be placed securely over the non-dominant arm. Participants also will be given a diary to record physical activity or psychological events that occur over the 24-h period that may influence BP measurements. Ambulatory BP recordings will be analyzed for mean 24-h, daytime, and nighttime SBP and DBP.

#### Vascular endothelial function

FMD_BA_, i.e., endothelium-dependent dilation to a flow stimulus, is the “gold standard” non-invasive measure of conduit artery NO-mediated endothelial function (Doshi et al., 2001; Seals et al., 2011). FMD_BA_ will be determined using high-resolution ultrasonography (Canon Xario 200) and analyzed with a commercially available software package (Vascular Analysis Tools 5.10.9, Medical Imaging Applications, LLC). Brachial artery diameter and blood flow velocity will be measured at baseline and for 2 min following reactive hyperemia induced by 5 min of forearm blood flow occlusion (upper forearm cuff placement). Data will be expressed both as a percent and absolute (millimeter) change in brachial artery diameter from baseline (pre-cuff inflation diameter). Peak and area under the curve shear rate will be calculated, and if group- or condition-differences exist, FMD_BA_ will be adjusted accordingly (Harris et al., 2010). Endothelium-independent dilation will be determined by measuring brachial artery dilation for 10 min after sublingual nitroglycerin (0.4 mg dissolvable tablet) to assess vascular smooth muscle sensitivity to NO (Seals et al., 2011).

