#### Randomization and Blinding

After baseline assessments, participants will be randomized to 3 months of high-resistance IMST or aerobic exercise training. Block randomization will be employed based on age (≤64 years versus ≥65 years) and baseline SBP (elevated BP/stage 1 hypertension: 120–139 mmHg versus stage II hypertension: ≥140 mmHg) (Whelton et al., 2018). Randomization will be performed by a professional research assistant not involved with data analysis who will remain unblinded for the duration of the study. Investigators responsible for collection and analysis of outcome measures will be blinded to participant group assignment. Given the design of this study comparing different lifestyle interventions, participant blinding is not possible.

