#### Statistical design, power, and analysis plan

Sample size calculations and pre-determined statistical power for this randomized, single-blind, parallel group design clinical trial are based on the results from the estrogen-deficient postmenopausal women enrolled in our IMST pilot study (Craighead et al., 2021b) and results from a meta-analysis on the effects of aerobic exercise on SBP in our target population (Kelley, 1999).

Accordingly, it was estimated that aerobic exercise reduces casual SBP by 3.0 ± 3.7 mmHg (mean ± standard deviation), while high-resistance IMST reduces casual SBP by 7.6 ± 7.4 mmHg. With these parameters, it was estimated that 36 subjects per group (72 total) would provide 90% power to detect a difference in the change in casual SBP between groups with a two-sided type I error rate of *p* = 0.05. To account for a potential dropout rate of ∼20%, we will enroll 45 participants into each group (90 participants total).

Block randomization by age (midlife: ≤64 years; older ≥65 years) and baseline SBP (elevated SBP/stage 1 hypertension: 120–139 mmHg; stage 2 hypertension: ≥140 mmHg) will be employed. Data for all outcome variables will be collected at baseline and at the end of the respective 3-month interventions. In addition, casual BP, 24-h BP and FMD_BA_ will be collected after abstaining from the interventions for 6 weeks to assess potential persistent effects of previous training on these outcomes.

Descriptive statistics will be calculated for all baseline and outcome variables. Means and standard deviations will be calculated for all continuous variables, and frequency and proportion will be provided for all categorical variables. Data transformation will be performed if appropriate. The 95% confidence interval will be calculated as needed.

Repeated measures analysis by linear mixed effects models will be used to assess changes in casual and 24-h BP and FMD_BA_. Data from baseline, end-intervention and 6 weeks after completing the intervention will be included in the model. Based on this model, comparisons in the changes in BP between the two groups will be performed to assess the treatment effect. The basic model will include group, measurement timepoint, and the group by time interaction. Potential confounders such as time post menopause or use of antihypertensive medications can be included for adjustment purposes.

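### The flow-mediated dilation result is shear-adjusted only if shear is seen to differ, so the trial's own post-randomisation data choose which effect is estimated

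*Protocol article*

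**What the plan says.** In the Protocol article, under Vascular endothelial function, shear comes from the FMD test itself: "Brachial artery diameter and blood flow velocity will be measured at baseline and for 2 min following reactive hyperemia". Two summaries are taken ("Peak and area under the curve shear rate will be calculated"), and the rule follows directly: "if group- or condition-differences exist, FMD_BA_ will be adjusted accordingly". A source is cited for it. FMD is reported on two scales: "Data will be expressed both as a percent and absolute (millimeter) change in brachial artery diameter".

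The timing is given elsewhere. Under Randomization and Blinding: "After baseline assessments, participants will be randomized to 3 months of high-resistance IMST or aerobic exercise training". Under Outcomes, all outcomes are measured before and after the 3 months, and "Casual SBP, 24-h SBP and FMD_BA_ also will be measured 6 weeks after cessation of IMST and aerobic exercise". So one FMD test precedes randomisation and two follow it.

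The analysis section (Statistical design, power, and analysis plan) states: "Repeated measures analysis by linear mixed effects models will be used to assess changes in casual and 24-h BP and FMD_BA". On its content: "The basic model will include group, measurement timepoint, and the group by time interaction". Time since menopause and antihypertensive use are offered as optional covariates. Shear is not mentioned there.

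**The concern.** The two sections describe two different quantities. The mixed model with group, time and their interaction estimates the total effect of assignment to inspiratory muscle strength training (IMST) rather than aerobic exercise on FMD, by whatever route. FMD adjusted for shear estimates the difference that would remain if the arms had the same shear. Both can be worth knowing. The protocol lets the observed shear data choose between them and does not say which is the main result.

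For the between-arm contrast, shear at 3 months and at follow-up may itself have been altered by training. A difference caused by training is part of the total effect, and it is also what makes the rule fire. The adjustment is thus most likely to be applied in the trials where it changes the answer most. The shift can go towards or away from zero, depending on which arm has more shear. What is at stake is the interpretation of one secondary outcome. FMD change also feeds the planned regression and mediation analyses, so an unclear choice could carry into them.

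**Working it through.** **1. The plan's own figure.** The article gives no power for FMD. Its sample size is for casual systolic pressure: changes of 3.0 (SD 3.7) and 7.6 (SD 7.4) mmHg, two-sided 0.05, 90% power, 36 per group.
- Difference: 7.6 − 3.0 = 4.6. Root-mean-square SD: √[(3.7² + 7.4²)/2] = 5.85.
- Normal approximation: 34 per group, with 91.6% power at 36. Noncentral t at 36: 90.5% (Welch) to 90.8% (pooled).
- Dropout: 36/(1 − 0.20) = 45 per group, 90 in all.

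The stated figures reproduce, so 36 per arm is used below.

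**2. Size of shift when the rule just fires.** Assumptions, none of them in the article: the trigger is a t-test on shear at p<0.05; adjustment is a single-time-point covariate analysis; the within-arm FMD-shear correlation r is 0.3 to 0.5.
- Smallest significant shear difference: t(0.975, 70) × √(2/36) = 1.994 × 0.2357 = 0.470 SD.
- Shift in the FMD contrast ≈ r × 0.470, which is 0.14 SD at r = 0.3, 0.19 at 0.4 and 0.24 at 0.5.

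This is a rough size. The fitted slope varies from sample to sample, so a shift can be smaller. In a simulation of the same set-up (shear shifts of 0, 0.5 or 0.8 SD), 15 to 38% of the trials in which the rule fired at r = 0.3 moved by less than 0.14 SD. At r = 0.5 the share below 0.24 SD was smaller, but at least 5%.

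**3. Behaviour of the rule over repeated trials.** Simulation with 36 per arm and 5,000 runs per row. Shear = shift × arm + noise (SD 1). FMD has within-arm SD 1, slope r on shear and the total arm effect shown. Adjusting always gives, in expectation, total − r × shift; for example 0.70 − 0.5 × 0.5 = 0.45. The conditional rule falls between that and the total.

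| Total effect (SD) | r | Shear shift (SD) | Rule fires | Unadjusted: mean, rejects | Always adjusted: mean, rejects | Conditional rule: mean, rejects |
|---|---|---|---|---|---|---|
| 0 | 0.5 | 0 | 4.9% | 0.00, 4.9% | 0.00, 5.3% | 0.00, 4.4% |
| 0.70 | 0.5 | 0 | 5.0% | 0.71, 83.3% | 0.71, 92.0% | 0.71, 84.3% |
| 0.70 | 0.3 | 0.5 | 55.9% | 0.71, 84.0% | 0.56, 65.1% | 0.59, 69.1% |
| 0.70 | 0.5 | 0.5 | 54.9% | 0.70, 83.0% | 0.45, 55.0% | 0.52, 61.6% |
| 0.70 | 0.3 | 0.8 | 91.9% | 0.70, 83.3% | 0.46, 46.0% | 0.47, 47.7% |
| 0.70 | 0.5 | 0.8 | 91.3% | 0.70, 83.7% | 0.30, 26.4% | 0.32, 28.1% |
| 0 | 0.5 | 0.5 | 55.0% | 0.00, 4.7% | −0.25, 21.1% | −0.19, 13.3% |

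With no effect on shear, the rule fires in about 5% of trials and causes no bias. With an effect on shear, its average is neither the total effect nor the equal-shear effect but a mixture, weighted by how often the rule fires.

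**The case against.** The strongest defence is physiological. FMD is dilation in response to a flow stimulus, and shear is that stimulus. If one arm receives a larger stimulus, raw FMD may misstate endothelial function, which is what the trial sets out to compare. A reader might infer from this point that shear adjustment is itself an error. The article does not support that: shear-adjusted FMD is a legitimate separate quantity, and a source is cited for it. Likewise, the 13.3% rejection rate is an error only against the null of no total effect, because the effect at equal shear is non-zero by construction in that scenario. This part of the defence stands. It does not justify letting the observed shear decide which quantity is reported.

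The trigger also covers condition differences, which may include saline versus vitamin C. That is a within-person comparison, so the post-randomisation argument does not apply to it in the same way. A baseline shear difference would also be pre-randomisation. And if the rule fires on a change over time common to both arms, the between-arm contrast need not move materially. The point is therefore confined to the between-arm contrast after baseline.

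The article gives no shear data and does not claim that either intervention alters shear, so systematic bias is a possibility and has not been shown. Nor does it say that unadjusted results would be withheld. The threshold, shear metric and method of adjustment may sit in the full analysis plan or the cited source, so their absence from an article is not held against it. Finally, the illustration uses one time point, whereas the planned model uses three. There the shift depends on the change in shear and the within-person slope.

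**Conclusion.** The point holds for the between-arm FMD comparison. The article states a rule under which observed shear, post-randomisation at two of the three FMD assessments, selects between a total effect and an effect at equal shear.

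Its size is conditional. If shear is unaffected by training, the rule is close to harmless. If training shifts shear by 0.5 to 0.8 SD and r is 0.3 to 0.5, a true total effect of 0.70 SD is estimated on average at 0.59 down to 0.32 SD. Power falls from about 83-84% to between 69% and 28%. All these inputs, including the p<0.05 trigger, are assumptions.

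A reader might take 0.14 to 0.24 SD as the least that the contrast can move once the rule fires. It is only the rough size at the edge of firing. A reader might also suppose that the trial's main conclusion is at risk. It is not, because FMD is a secondary outcome, and the casual systolic pressure analysis and the sample size are untouched.

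**What to change.** In Vascular endothelial function, remove the condition that differences must exist before adjusting, as far as the between-arm comparison is concerned. Replace it with two statements:

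- The main between-arm FMD analysis is unadjusted for shear and comes from the mixed model in the statistical section, whatever the shear comparison shows.
- One shear-adjusted analysis, with one shear metric and one method chosen before the data are seen, is always reported as supportive. It is labelled as an effect at equal shear and not as the total treatment effect.

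Area-under-the-curve shear as a covariate in the same model would serve, but fixing the choice matters more than which metric is chosen. Within-person condition comparisons, such as the vitamin C test, can have their own fixed rule. The cost is a sentence or two of text and one extra table from data already being collected.
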